## Abstract

**Background:**

Coronary computed tomography angiography (CCTA) is widely used in the diagnostic work-up of patients with stable chest pain. CCTA has an excellent negative predictive value, but a moderate positive predictive value for detecting coronary stenosis. Computed tomography-derived fractional flow reserve (FFRct) is a non-invasive, well-validated technique that provides functional assessment of coronary stenosis, improving the positive predictive value of CCTA. However, to determine the value of FFRct in routine clinical practice, a pragmatic randomised, controlled trial (RCT) is required. We will conduct an RCT to investigate the impact of adding FFRct analysis in the diagnostic pathway of patients with a coronary stenosis on CCTA on the rate of unnecessary invasive coronary angiography, cost-effectiveness, quality of life and clinical outcome.

**Methods:**

The FUSION trial is a prospective, multicentre RCT that will randomise 528 patients with stable chest pain and anatomical stenosis of ≥ 50% but < 90% in at least one coronary artery of ≥ 2 mm on CCTA, to FFRct-guided care or usual care in a 1:1 ratio. Follow-up will be 1 year. The primary endpoint is the rate of unnecessary invasive coronary angiography within 90 days.

**Conclusion:**

The FUSION trial will evaluate the use of FFRct in stable chest pain patients from the Dutch perspective. The trial is funded by the Dutch National Health Care Institute as part of the research programme ‘Potentially Promising Care’ and the results will be used to assess if FFRct reimbursement should be included in the standard health care package.

**Supplementary Information:**

The online version of this article (10.1007/s12471-022-01711-w) contains supplementary material, which is available to authorized users.

## Background

In the Netherlands, 180,000 new patients present with stable chest pain—the most common symptom of coronary artery disease (CAD)—annually [1]. In the past few years, the preferred diagnostic strategy in these patients has evolved from a focus on functional testing to coronary computed tomography angiography (CCTA) [2, 3]. Treating cardiologists in the Netherlands are recommended to apply a more consistent management by using a single non-invasive first-line test for diagnosing CAD due to current variation in clinical practice [1]. Implementation of CCTA in the work-up of patients with stable chest pain, however, may lead to unnecessary invasive testing, because CCTA has the ability to accurately rule out CAD [4, 5], but not the ability to correctly predict a haemodynamically significant stenosis on invasive coronary angiography (ICA) [6].

Computed tomography-derived fractional flow reserve (FFRct) may overcome the shortcomings of CCTA. FFRct is a non-invasive method that uses the already acquired CCTA images as the basis to calculate coronary FFR values as they would be expected if measured invasively (see Fig. S1 in Electronic Supplementary material). FFRct applies computational fluid dynamics and deep-learning image-based modelling to estimate rest and hyperaemic coronary flow and pressure from CCTA [7]. FFRct represents the ratio of maximal coronary blood flow through a stenotic artery to the blood flow in the hypothetical case that the artery is normal [8]. Early validation studies, assessing the diagnostic performance of FFRct with invasive FFR as the reference standard, are promising. On a per vessel analysis, the sensitivity is 80–88% and the specificity is 61–86% [9–11].

So far, observational data have shown that FFRct adds to the diagnostic strategy in patients with stable chest pain by reducing the rate of unnecessary ICA (defined as ICA showing unobstructed coronaries). The ADVANCE registry indicated that the availability of FFRct as an adjunct to CCTA would change the management of CAD in 66.9% of patients when compared with an initial CCTA-based treatment plan [12, 13]. This study also demonstrated the safety of patient management following the implementation of FFRct into the decision pathway, and the avoidance of invasive assessment in most patients with a negative FFRct [12, 13]. The PLATFORM study demonstrated a cancellation of ICA in 61% of CCTA + FFRct patients. No adverse clinical events occurred at 1 year in these patients, indicating safe deferral of ICA based on CCTA and FFRct [14]. The recent FORECAST trial showed that a strategy of CCTA with selective FFRct in stable angina patients did not differ significantly from standard clinical care pathways in cost and clinical outcomes, but did reduce the use of other non-invasive tests and ICA [15]. These studies suggest that FFRct can alter the management of patients and safely reduce the percentage of patients referred for ICA without significant CAD. An overview of the main findings of these current studies is presented in Tab. 1.

**Table 1 Tab1:** Main characteristics of the studies on the use of FFRct in patients suspected with CAD

Study, year	First author	Study design	Sample size, *n*	Main results
*The ADVANCE registry, 2018, 2020*	Fairbairn et al.[13] and Patel et al. [12]	Pragmatic, prospective, international, multicentre registry of patients being investigated for clinically suspected CAD with documented stenosis of at least 30% on coronary CTA	5083	– FFRct modified treatment recommendation in 66.9% of the patients when compared with CCTA alone, was associated with less negative ICA, predicted revascularisation, and identified subjects at low risk of adverse events through 90 days. – 1-year outcomes show low rates of events in all patients, with less revascularisation and a trend toward lower MACE and significantly lower cardiovascular death or MI in patients with a negative FFRct compared with patients with abnormal FFRct values
*The PLATFORM study, 2015, 2016*	Douglas et al. [14, 23]	Prospective, consecutive cohort study with a comparative effectiveness observational design in symptomatic outpatients without known CAD, but with an intermediate likelihood of obstructive CAD, whose physician had planned non-emergent, non-invasive, or invasive cardiovascular testing to evaluate suspected CAD	584	– Among those with intended ICA (FFRct-guided = 193; usual care = 187), no obstructive CAD was found at ICA in 24 (12%) in the CTA/FFRct arm and 137 (73%) in the usual care arm. Invasive coronary angiography was cancelled in 61% after receiving CTA/FFRct results. Clinical event rates within 90 days were low in usual care and CTA/FFRct arms. – 1-year outcomes show that in patients with planned ICA, care guided by CTA and selective FFRct was associated with equivalent clinical outcomes and quality of life, and lower costs, compared with usual care over 1‑year follow-up
*The FORECAST trial, 2021*	Curzen et al. [15]	Open-label, multicentre, randomised, controlled clinical trial. Patients presenting at RACP, who require a cardiac test, were randomised to either routine care (management strategy based on NICE Chest Pain of Recent Onset Guidance—CG95) or CCTA with selective FFRct group in a 1:1 ratio	1400	A strategy of CCTA with selective FFRct in patients with stable angina did not differ significantly from standard clinical care pathways in cost or clinical outcomes, but did reduce the use of non-invasive testing and ICA, which was 22% lower in the experimental group
*Sub-study of the CRESCENT I and II trials, 2020*	Nous et al. [24]	Secondary analysis using the CCTA data. Observational cohort study, which included patients with suspected CAD and a ≥ 50% stenosis on CCTA who had been randomised to cardiac CT in the CRESCENT I trial and II trials	372	The availability of FFRct would have reduced the number of patients requiring additional testing by 57%-points compared with CCTA alone. The initial management strategy would have changed for 30 patients. Reserving ICA for patients with a FFRct ≤ 0.80 would have reduced the number of ICA following CCTA by 13%-points

*CAD* coronary artery disease, *CCTA* coronary computed tomography angiography, *FFRct* computed tomography-derived fractional flow reserve, *ICA* invasive coronary angiography, *RACP* rapid access chest pain clinic

Prior FFRct studies involved populations of various countries with different work-up and were based on a non-randomised design with the exception of the FORECAST trial [13, 14]. There are no prospective data on the real-world use of FFRct in the Dutch population of stable chest pain patients. On top of that, there are no trials that randomise patients who have undergone CCTA to standard care or FFRct-guided care based on the presence of > 50% stenosis on CCTA.

The ‘Addition of FFRct in the diagnostic pathway of patients with stable chest pain to reduce unnecessary invasive coronary angiography’ (FUSION) trial is a multicentre, randomised, controlled trial that investigates the impact of adding FFRct analysis in the diagnostic pathway of stable chest pain patients with a 50–90% coronary stenosis on CCTA, on the rate of unnecessary ICAs, the cost-effectiveness, quality of life and clinical outcomes.

The FUSION trial is sponsored by the Dutch Ministry of Health and the Dutch National Health Care Institute (*Zorginstituut Nederland*) as part of the research programme ‘Potentially Promising Care’ (‘Veelbelovende Zorg’) that aims to assess medical technology to determine if it can be reimbursed in the standard health care package.

## Methods

### *Study design and population*

The FUSION trial is an investigator-initiated, multicentre, randomised, controlled trial in the Netherlands enrolling 528 patients with stable chest pain and 50–90% stenosis in at least one coronary artery ≥ 2 mm on CCTA. CCTA is performed for clinical indications, therefore CCTA itself is not part of the study procedures. The inclusion and exclusion criteria are presented in Tab. 2. Patients will be randomised on a 1:1 basis to receive FFRct-guided care or usual care, and will be followed up for a minimum of 1 year. Fig. 1 provides a flow chart illustrating the overview of the study design. The trial will start in 7 Dutch hospitals: Erasmus Medical Centre, University Medical Centre Groningen, University Medical Centre Utrecht, Adrz Hospital, Gelre Hospital, St. Jansdal Hospital, and Martini Hospital Groningen. Additional centres may join after the trial commences.

**Table 2 Tab2:** Inclusion and exclusion criteria

Inclusion criteria	Exclusion criteria
Age ≥ 18 years	Inability to provide informed consent
Stable chest pain	Unstable angina/acute coronary syndrome
Underwent CCTA with ≥ 50% but less than 90% stenosis in at least one major epicardial vessel with a diameter ≥ 2 mm	Unstable clinical status
	Expected inability to complete follow-up and comply with follow-up aspects of the protocol
	History of coronary revascularisation
	Non-invasive or invasive diagnostic testing for CAD within the past 12 months (with the exception of exercise ECG)
	Unsuitable for revascularisation if required (for example due to comorbidities or anatomical features)
	Poor CT quality with expected inability to perform FFRct analysis

*CAD* coronary artery disease, *CCTA* coronary computed tomography angiography, *ECG* electrocardiogram, *FFRct* computed tomography-derived fractional flow reserve

**Fig. 1 Fig1:**
[figure not shown]
Flow chart of the study design. * Clinicians are strongly discouraged from referring these patients for ICA. ** Patients are expected to be treated medically, but there may be instances whereby the clinician overrules this decision. *** Clinicians are encouraged to schedule ICA if coronary revascularisation is considered advisable. **** Decision for ICA depends on symptomatology, stenosis and FFRct location, extent of CAD, number of coronary arteries involved, and comorbidities. In some cases, one may first treat the patient medically to see if the complaints of chest pain disappear. *CAD* coronary artery disease, *CCTA* coronary computed tomography angiography, *FFRct* computed tomography-derived fractional flow reserve, *ICA* invasive coronary angiography

### Study procedures

#### The intervention group (FFRct group)

In the intervention group, FFRct analysis will be performed based on the available CCTA data, without the need of additional imaging, radiation or medication. FFRct will be performed by HeartFlow, Inc. (Redwood City, California, United States) in all patients. A secure web transfer portal will be established with each site allowing transfer of the CCTA data to HeartFlow for FFRct analysis. The FFRct output will be returned to the investigating site within 1 working day [9]. Subsequently, the patient management strategy is determined with incorporation of the FFRct results (Fig. 1). In principle, patients with a negative FFRct (FFRct of > 0.80) should undergo conservative management. Patients with a positive FFRct (FFRct ≤ 0.80 for one or more focal stenoses in any coronary artery ≥ 2 mm) should undergo subsequent ICA.

#### The control group (usual care group)

All patients in the control group will undergo usual care. In case of an anatomical stenosis on CCTA, this often leads to ICA and invasive FFR measurement. The indication for ICA and revascularisation is at the discretion of the treating physician. It is recommended that the treating physician follows the European Society of Cardiology guidelines for the diagnosis and management of chronic coronary syndrome [2].

#### Post-hoc FFRct analysis in usual care group

Since in the intervention group, patients with FFRct > 0.80 will in principle not undergo ICA, false negative FFRct cases remain unidentified. Therefore, FFRct will also be performed in the usual care group (post-hoc FFRct), but will neither be revealed to the clinical site nor influence the diagnostic pathway. The treating clinician will be blinded to these FFRct results. This way, we can indirectly gauge the number of false negative FFRct findings retrospectively in patients who underwent ICA in the control group without influencing patient management in this group. A false negative is defined as negative FFRct result with an ICA showing haemodynamically significant stenosis on invasive FFR.

Data to be collected at baseline, 90 days and 1 year are presented in Electronic Supplementary Material.

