### Study endpoints

The primary endpoint is the rate of unnecessary ICA occurring within 90 days in both groups as determined on a per patient level. Unnecessary ICA is defined as any ICA without haemodynamically significant CAD. The leading indicator for the evaluation of significant CAD is the functional measurement (FFR/iFR). If functional measurements are not available, then significant CAD is indicated by quantitative coronary angiography. Primary and secondary endpoints definitions are listed in Fig. S2 in Electronic Supplementary Material.

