#### Cost-effectiveness analysis

We will perform a cost-utility analysis in accordance with the Dutch guidelines for economic evaluations in health care (*Zorginstituut 2016*) from the societal and the health care perspective. A cost (EUR) and outcomes (quality-adjusted life-year) comparison between the FFRct and the usual care groups as observed in the RCT for the 1‑year time frame will be made. Next, a state-transition model will be built to calculate the cost-effectiveness of FFRct considering a long-term time horizon. In this model we will synthesise data from the RCT with the post-hoc results of FFRct in the usual care group and literature data.

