Similar to the design of the CRESCENT trial [17], the FUSION trial design is based on improving the diagnostic strategy of stable angina pectoris patients and not merely on identifying which diagnostic test is superior. In the FUSION trial, we focus on patients in whom we expect FFRct to be most appropriate, namely patients with intermediate anatomic stenosis. On top of that, we have designed our study in such a way that we can estimate the number of false negative FFRct results and determine the effects of missing CAD diagnosis, by performing a post-hoc FFRct analysis in the control group based on the existing CCTA in each patient. The patients in the control group undergo routine care, which is not based on FFRct but, mostly, on ICA. This ensures that we can determine how often the FFRct results would have led to a false negative result. In the intervention group, patients with FFRct > 0.80 will include both the true and false negatives, and we will assess the outcome of these patients. These results combined will provide solid data on how often false negatives occur and what the consequences are. We will be able to make an assumption on the maximum risk these patients have for developing major adverse cardiac events in 1 year.

Major adverse cardiac events is not selected as the primary endpoint, as it would require a very high number of patients to be included in the trial. Since we can make accurate assumptions of the risk of major adverse cardiac events in the study population—and unnecessary ICAs is a clinically relevant endpoint—we have chosen the latter as the primary endpoint.

The FUSION trial has been designed to investigate the role of FFRct in the diagnostic strategy of patients with stable chest pain after CCTA and does not have the potential to answer questions about optimal treatment strategy in patients with symptomatic CAD. This was subject of the ISCHEMIA trial, which results support that the vast majority of patients with CAD (in a selected population of patients with an abnormal functional test) can be treated with an initial conservative strategy of medical therapy alone [21]. These results do not undermine the prominent role of functional testing in the management of stable chest pain patients, whether this should be based on functional testing or based on FFR testing, such as in the FUSION trial.

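### The FFRct false-negative count is only a lower bound and its rate is biased in an unknown direction, yet the Discussion says the design can determine the frequency

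*Protocol article*

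**What the plan says.** The section on post-hoc FFRct in the usual care group explains that false negatives stay hidden in the intervention arm, because FFRct-negative patients there will in principle not have ICA. FFRct is therefore also run, unseen, in the controls, so that "we can indirectly gauge the number of false negative FFRct findings retrospectively in patients who underwent ICA in the control group". The counting rule is: "A false negative is defined as negative FFRct result with an ICA showing haemodynamically significant stenosis on invasive FFR".

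Study endpoints defines significant CAD for the primary endpoint differently. The functional measurement, FFR or iFR, leads, and "If functional measurements are not available, then significant CAD is indicated by quantitative coronary angiography".

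On who gets ICA in the control arm, the control group section says "The indication for ICA and revascularisation is at the discretion of the treating physician", and describes the usual course without a proportion: "In case of an anatomical stenosis on CCTA, this often leads to ICA and invasive FFR measurement".

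Two places rely on the result. The Discussion states: "This ensures that we can determine how often the FFRct results would have led to a false negative result", and goes on to call the combined data solid. The Cost-effectiveness analysis says of the long-term model that "we will synthesise data from the RCT with the post-hoc results of FFRct in the usual care group and literature data".

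**The concern.** Two features of the definition limit what the post-hoc analysis can show.

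First, the article uses two reference standards for what looks like one concept and does not explain why. A patient can have significant CAD when the primary endpoint is judged and yet not count as missed by FFRct.

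Second, disease status is known only in controls whom a physician chose to send for ICA. This is partial, non-random verification, and the article describes no allowance for it.

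The stakes are the article's statement of how often FFRct would miss disease, and one input to a long-term model in a trial whose results will inform a reimbursement decision. The primary endpoint, its analysis and the sample size are not affected.

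**Working it through.** The article states no false-negative count or rate, so there is no figure to reproduce. The check compares the definitions and then illustrates their effect.

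**Step 1. The same patient under both definitions (FFRct negative, control arm)**

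| Patient | Primary endpoint | False-negative rule |
|---|---|---|
| ICA, significant on invasive FFR | ICA necessary | counted |
| ICA, significant on iFR, no FFR | ICA necessary | not counted |
| ICA, no functional measurement, significant on QCA | ICA necessary | not counted |
| Significant CAD, no ICA | no ICA to classify | never verified |

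Only the first row is counted. The count therefore cannot exceed the true number, and it falls short whenever a patient belongs to another row.

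**Step 2. Inputs for an illustration**

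- From the article: 264 controls (Sample size calculation); sensitivity Se 80–88% and specificity Sp 61–86% (Background). These are per-vessel figures, used here as if per patient.
- Assumed, not in the article: two strata of 132 with significant disease in 40% and 80%; ICA in 50% and 90% of them; invasive FFR obtained in a share f = 1, 0.7 or 0.5 of the false negatives at ICA.

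**Step 3. Count**

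- True false negatives = 132 × (0.40 + 0.80) × (1 − Se) = 158.4 × (1 − Se): 31.7 at Se 0.80, 19.0 at Se 0.88.
- Of these, at ICA = 132 × (0.40 × 0.50 + 0.80 × 0.90) × (1 − Se) = 121.44 × (1 − Se): 24.3 and 14.6.
- Counted = f × the line above: 24.3, 17.0 or 12.1 at Se 0.80; 14.6, 10.2 or 7.3 at Se 0.88.

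Using the primary endpoint's hierarchy would recover the gap between 12.1 and 24.3 (if iFR or QCA identifies those cases), but not the gap between 24.3 and 31.7.

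**Step 4. Share of FFRct-negative patients with disease**

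True negatives = 132 × (0.60 + 0.20) × Sp = 105.6 × Sp in all controls, and 132 × (0.60 × 0.50 + 0.20 × 0.90) × Sp = 63.36 × Sp at ICA.

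| | Se 0.80, Sp 0.61 | Se 0.88, Sp 0.86 |
|---|---|---|
| All FFRct-negative controls (truth) | 31.7 / (31.7 + 64.4) = 0.330 | 19.0 / (19.0 + 90.8) = 0.173 |
| ICA patients, FFR in all | 24.3 / (24.3 + 38.6) = 0.386 | 14.6 / (14.6 + 54.5) = 0.211 |
| FFR-positive cases over all FFRct-negative ICA patients, f = 0.5 | 12.1 / 62.9 = 0.193 | 7.3 / 69.1 = 0.106 |

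The second row overstates the truth, because ICA is assumed to be aimed at higher-risk patients. The third understates it, because patients without FFR stay in the denominator but cannot enter the numerator. If patients without FFR leave both, and FFR use is equal in those with and without disease, f cancels and the second row returns. The sign of the bias thus depends on the denominator and on selection.

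**Step 5. Sensitivity**

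With equal accuracy in both strata, sensitivity among ICA patients is unbiased: 1 − 24.3 / 121.44 = 0.80. With assumed stratum sensitivities of 0.75 and 0.88, the truth is 1 − 25.9 / 158.4 = 0.837 and the ICA patients give 1 − 18.0 / 121.44 = 0.852, a slight overstatement.

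**The case against.** The other side has real arguments.

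- *FFR-only is defensible.* FFRct estimates invasive FFR, and the Background describes its validation against that standard. QCA is anatomical, so counting FFRct-negative, QCA-positive patients as errors could label stenoses without haemodynamic effect as missed disease. The primary endpoint has to classify every ICA and so needs a fallback; an accuracy analysis does not. This stands, and it is why the two sections are better called unreconciled than contradictory. It does not explain why iFR, a functional measurement of equal rank in Study endpoints, is left out, nor does it supply the denominator that an FFR-only analysis needs.
- *The limit is disclosed.* The post-hoc section calls the estimate indirect and names the ICA patients as its population. That is true of that section, but the Discussion drops the limit.
- *Blinding.* "The treating clinician will be blinded to these FFRct results", so FFRct cannot directly drive referral. This makes a correction based on recorded clinical variables more plausible, but it verifies nobody who had no ICA.
- *Other evidence.* The Discussion pairs this estimate with the followed outcomes of FFRct-negative intervention patients, and the post-hoc results are one of three model inputs. The estimate is therefore not the trial's only evidence on deferring ICA.
- *An article condenses.* The correction method may properly sit in the full protocol or SAP. The definition and the Discussion's claim are stated here.

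A reader might infer that the estimate must understate missed disease and so favours FFRct. The documents support this for the raw count only; step 4 shows a rate going either way. A reader might also apply 59–72% prevalence (the complement of the 28–41% in the Sample size calculation) to all 264 controls to size the loss. That figure describes patients who had ICA, and the article gives no proportion for FFR use, so no share lost can be derived.

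**Conclusion.** The point holds in limited form. As defined, the raw false-negative count is a lower bound on the number of FFRct-negative controls with significant CAD. Any rate among FFRct-negative patients rests on partial, non-random verification, with a bias whose direction is unknown and depends on the denominator chosen. The Discussion promises more than the post-hoc section claims or the design can deliver.

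The structural conclusion rests on the text alone. The figures (7.3 to 24.3 counted against 19.0 to 31.7 true; 0.386 or 0.193 against 0.330) show what can happen under assumed prevalence, ICA use and FFR use, and are not predictions. Importance is moderate at most: a secondary estimate and one model input are affected.

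**What to change.** 1. Reconcile the post-hoc section with Study endpoints. Include iFR, and report false negatives in two ways, each with its denominator:
   - on functional measurement only, among FFRct-negative controls with ICA and FFR or iFR;
   - on the full hierarchy of FFR/iFR and then QCA, among FFRct-negative controls with ICA.
2. Add an estimate for all FFRct-negative controls corrected for partial verification, with its confidence interval. Inverse-probability-of-verification weighting or multiple imputation would serve, using whichever baseline and CCTA variables are available. The data list is in a supplement not seen here, so availability has to be confirmed.
3. Carry the uncertainty of the corrected estimate into the state-transition model.
4. Reword the Discussion to say that the false-negative frequency will be estimated under stated assumptions.

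The cost is wording and modest analysis work, with no change to patient management. The downside is a wider and possibly less favourable false-negative estimate.
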